#### The National Immunisation Management System (NIMS) demographics

Testing data will be linked to NIMS demographic file to augment the National Health Service number in the testing data using combinations date of birth, surname, first name, and postcode using deterministic linkage with >95.5% uniqueness.

Following this the testing data will be linked using NHS number to the NIMS demographic file to include information on potential confounding variables related to targeted populations:

Gender, Ethnicity, NHS region, IMD Quintiles, and vaccine delivery priority groups: healthcare worker, CEV, care home resident, immunosuppression and “at risk” status.

#### Vaccination data- The National Immunisation Management System (NIMS)

Booster doses will be identified as being a third dose 175 days or more after a second dose and given after 13th September 2021.

Only individuals who are unvaccinated at the time of onset or who have had two or three doses of vaccine at the time of onset will be included. In addition, there must be an interval of at least 175 days from dose2 to dose3 or from dose 2 to onset. Individuals with a mix of vaccines in their primary schedule or less than 19 days between their first and second dose will be excluded.

Therefore, a booster is recognised as a booster if given at least 175 days after a second dose.

## Emergency Care Data Set (ECDS)

ECDS data include hospital admissions through NHS emergency departments in England but not elective admissions

- Testing data will be linked on NHS number and date of birth to an Emergency Care attendances that have resulted in an inpatient admission.
- Attendances within 14 days of the positive test
- Exclude injury related attendances

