## 2. Objectives

### 2.1. Aim

To estimate the effectiveness of COVID-19 booster vaccines against covid-19 related symptoms, hospitalisation and death in adults aged 18-49 years and 50 years and older

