### 2.2. Primary objectives

- I. Relative VE of each booster vaccine by primary course vaccine type against symptomatic disease compared to 2 doses
- II. Relative VE of each booster vaccine by primary course vaccine type against hospitalisation following symptomatic disease compared to 2 doses
- III. Relative VE of each booster vaccine by primary course vaccine type against death following symptomatic disease compared to 2 doses

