#### 3.2. Data sources

COVID-19 testing data.

- SARS-CoV-2 Testing Polymerase-chain-reaction (PCR) positive and negative tests from the 08 December 2020 to date of extraction for individuals aged  $\geq 18$  years from the UKHSA Unified Sample Database.
- Exclude any negative tests taken within 7 days of a previous negative test, or where symptoms were recorded, with symptoms within 10 days of symptoms for a previous negative test (likely represent the same episode).
- Exclude any negative tests within 21 days before a positive test (false negatives)
- Exclude any positive and negative tests within 90 days of a previous positive test
- Participants contribute a maximum of one randomly chosen negative test result in the booster follow-up period.
- Data are restricted to persons who had reported symptoms and gave an onset date.
- Samples must be within 10 days after symptom onset (account for reduced sensitivity of PCR testing beyond this period).
- Exclude any positive samples sequenced and found not to be the Delta variant

After these criteria, as applied samples taken from 13 September 2021 (week 37, 2021) will be retained for analysis.

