### 3.6. Outcomes

- Individuals testing positive for SARS-CoV-2 on PCR who reported symptoms within the preceding 10 days
- Individuals testing positive for SARS-CoV-2 on PCR who report symptoms and have a hospital admission from ECDS within 14 days of testing.
- Individuals testing positive for SARS-CoV-2 on PCR who report symptoms and die within 28 days of testing.

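### The hospitalisation outcome needs no COVID-19 or respiratory reason and no stated order after symptom onset, so hospital VE is pulled toward symptomatic VE and takes on part of its waning

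*Protocol*

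**What the plan says.** The aim in section 2.1 is the "effectiveness of COVID-19 booster vaccines against covid-19 related symptoms, hospitalisation and death". Primary objective II in section 2.2 puts the events in order: VE "against hospitalisation following symptomatic disease compared to 2 doses".

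The operational rules are looser. The ECDS part of section 3.2 takes emergency attendances that resulted in an inpatient admission, with the window "Attendances within 14 days of the positive test" and one restriction on cause, "Exclude injury related attendances". Section 3.6 defines the outcome as people who test positive, report symptoms and "have a hospital admission from ECDS within 14 days of testing". Neither place names a COVID-19 or respiratory reason, and neither places the admission relative to onset.

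Other parts of the protocol narrow the outcome. The data come from Pillar 2 community testing (section 1), only symptomatic people with an onset date are kept, and "Samples must be within 10 days after symptom onset" (section 3.2). On the type of admission, "ECDS data include hospital admissions through NHS emergency departments in England but not elective admissions".

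Section 3.5 divides follow-up after a BNT162b2 booster into bands that include 14-34 and 35-69 days and, for the BNT162b2-primed group, 70 days or more. Section 7 gives the assessment of possible waning as the reason for these bands. The limitations in section 4 do not mention unrelated admissions.

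**The concern.** A symptomatic positive person who is admitted as an emergency for another reason, for example a cardiac event, within the window counts as a hospital case. To become such a case, the person needs only the infection and a background admission. If the booster does not change the background admission rate, its effect on these cases is its effect on symptomatic infection, not its effect on severe disease.

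Hospital VE is then a weighted average of the two effects. When symptomatic VE declines with time since booster, hospital VE declines too, even if protection against severe disease is constant. Whether protection against hospitalisation lasts is a main question that readers will bring to the post-booster bands, and part of any decline could come from the outcome definition. The covariates in section 3.9 do not correct this, because the problem is in the classification of the outcome and not in confounding.

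**Working it through.** The protocol gives no expected VE, event count or unrelated share for this outcome, so there is no figure of its own to reproduce. Every numerical input below is an assumption except the 14-day window (sections 3.2 and 3.6) and the 10-day sampling limit (section 3.2).

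**Step 1. Mixture.** Let p be the share of hospital cases in the two-dose comparator whose admission is unrelated to COVID-19. Assume the background admission rate is the same in boosted and comparator positives. With the same test-negative controls for both components,

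OR(observed) = (1 − p) × OR(severe) + p × OR(symptomatic), and VE = 1 − OR.

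**Step 2. Effect of waning in symptomatic VE.** Hold severe-disease VE at 95%, so OR(severe) = 0.05, and let symptomatic VE be 80%, 60% and 40%. For p = 15%:

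- 80%: 1 − (0.85 × 0.05 + 0.15 × 0.20) = 92.75%
- 60%: 1 − (0.85 × 0.05 + 0.15 × 0.40) = 89.75%
- 40%: 1 − (0.85 × 0.05 + 0.15 × 0.60) = 86.75%

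| p | Sympt. VE 80% | 60% | 40% | Spurious fall |
|---|---|---|---|---|
| 0% | 95.0% | 95.0% | 95.0% | 0 points |
| 5% | 94.25% | 93.25% | 92.25% | 2 points |
| 15% | 92.75% | 89.75% | 86.75% | 6 points |
| 30% | 90.5% | 84.5% | 78.5% | 12 points |

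The fall is p times the fall in symptomatic VE, here p × 40 points.

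**Step 3. Plausible p.** Write b = r × 14/365.25 for the background admission risk over a 14-day forward window, with r an assumed yearly emergency admission rate and h an assumed COVID-19 admission risk among symptomatic comparator cases. Then p = b/(b + h).

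- r = 5%, h = 5%: b = 0.19%, p = 4%
- r = 10%, h = 2%: b = 0.38%, p = 16%
- r = 20%, h = 1%: b = 0.77%, p = 43%

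The 5% to 30% in the table therefore lies inside the range that these assumptions allow. The range is wide, and the protocol gives nothing to narrow it.

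**Step 4. Order of events.** Objective II has the admission following symptomatic disease. Sections 3.2 and 3.6 count 14 days from the test only. Since the sample may be up to 10 days after onset, an admission before the test can still follow onset and be genuine. Onset is therefore the lower bound that matches the objective.

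**The case against.** A reader might infer that the window runs 14 days either side of the test, so that admissions before the infection count. The text does not say this. The direction is unstated, and other sections point forward: objective II, the similar wording for deaths in section 3.2, where only a forward reading is possible, and section 3.4, which uses an earlier sample cut-off so that hospitalisations and deaths can be captured. The missing direction is mostly missing detail. Nor is an admission before the test necessarily unrelated, as step 4 shows.

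A reader might also infer that hospital VE will simply follow the waning of symptomatic VE. That would need p near 100%. At p = 15%, a 40-point fall in symptomatic VE gives 6 points. Planned admissions are not part of the problem either, because elective admissions are outside ECDS.

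Three further objections have weight. First, the symptomatic, community-testing, non-elective and non-injury restrictions all lower p. Second, the assumed fall to 40% has no support in the protocol: boosters began on 14 September 2021 and the bands were added on 6 December, 83 days later, so little follow-up beyond 70 days existed then. Third, waning of hospitalisation VE is not a listed objective, and a sensitivity analysis could sit in a separate analysis plan.

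These limit the size of the problem but do not remove it. The protocol itself defines the endpoint of a primary objective, and does so more loosely than the objective. None of the restrictions excludes an unrelated non-injury emergency near a mild infection. Section 7 does not exempt hospitalisation from the reason it gives for the bands.

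**Conclusion.** The point holds as a partial bias of unknown size. The outcome in sections 3.2 and 3.6 is any non-injury emergency admission near a positive test, while sections 2.1 and 2.2 ask about COVID-19 related hospitalisation after symptomatic disease. When symptomatic VE is below severe-disease VE, measured hospital VE is biased toward it and takes on about p times its waning.

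With severe-disease VE constant at 95% and symptomatic VE falling from 80% to 40%, the spurious fall is 2, 6 or 12 points for p of 5%, 15% or 30%. This rests on those assumed values and on equal background admission rates in boosted and comparator positives. It does not show that hospital VE in this study would be wrong by any particular amount. It shows that a decline of a few points across the bands could not be read as waning of protection against severe disease. This is a cheap improvement, not a flaw that undoes the design.

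**What to change.** 1. In sections 3.2 and 3.6, count attendances on or after symptom onset and up to 14 days after the test. This agrees with objective II and keeps genuine admissions that fall between onset and sampling. A lower bound at the test day would lose them. The window can then be up to 10 + 14 = 24 days long, so it settles the order of events but does not by itself reduce p.
2. Repeat the hospitalisation model with the outcome limited to attendances that have a COVID-19 or acute respiratory reason, where ECDS reason coding allows. The injury exclusion already needs some information on reason for attendance, but the protocol does not describe the coding, so its completeness must be checked first.
3. State that waning of hospitalisation VE will be concluded only if the restricted version agrees, and add unrelated admissions to the limitations in section 4.

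The cost is one further filter on linked data and one repeat of the model. The downside is fewer hospital cases, hence wider intervals in the later bands, and some true cases missed where coding is incomplete.

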## Deaths

- Deaths within 28 days of a positive test as recorded in the NIMS data (based on the NHS Patient Demographics Service)

### 3.3. Study population

All adults resident in England aged 50 years and older reporting symptoms and tested during the study period

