## 1. Background

This is the protocol for the assessing the effectiveness of COVID-19 booster doses in England using community testing through Pillar 2 and the test negative case control design. Many of the methods follow those used recently to assess waning of effectiveness for ChAdOx1-S (Vaxzevria, AstraZeneca) and Pfizer-BioNTech (BNT162b2/ Comirnaty®) vaccines (1).

In the UK, COVID-19 booster vaccines were introduced on 14 September 2021. The UK Joint Committee on Vaccination and Immunisation (JCVI) recommended either a BNT162b2 or a half dose (50µg) of mRNA-1273 (Spikevax, Moderna) vaccine to be given as a booster dose no earlier than 6 months after completion of the primary vaccine course (2).

The initial booster programme is currently for all adults over 50 and those 16-49 years with underlying health conditions that put them at higher risk of severe COVID-19, adult carers and adult household contacts (aged 16 or over) of immunosuppressed individuals, and healthcare workers. On the 30 November 2021 the booster vaccine programme was rolled out to all individual's aged 18 years and over.

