### 3.9. Statistical analysis

We will use a test-negative case-control design to estimate vaccine effectiveness of a booster dose of BNT162b2 vaccine against PCR-confirmed symptomatic disease, hospitalisation and death. Analysis will be by logistic regression with the PCR test result as the dependent variable where those

testing positive are cases and those testing negative controls. Vaccination status will include as an independent variable and effectiveness defined as 1- odds of vaccination in cases/odds of vaccination in controls. Estimates will be reported with 95% confidence intervals. Analyses will stratified by which primary doses had been received.

Vaccine effectiveness will be adjusted in logistic regression models for:

- age (5 year bands)
- sex
- index of multiple deprivation (quintile)
- ethnic group
- care home residence status
- geographic region (nhs region)
- period (calendar week of onset)
- health and social care worker status
- clinical risk group status
- clinically extremely vulnerable
- severely immunosuppressed
- previously testing positive

These factors will all be considered potential confounders so will be included in all models.

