## 7. Changes to the analysis plan between version 2.1 (the final version before the first booster analysis) and 2.2 (current version)

| Change                                                                            | date       | Reason                                                                                                                                                              |
|-----------------------------------------------------------------------------------|------------|---------------------------------------------------------------------------------------------------------------------------------------------------------------------|
| Addition of 18-49 analysis                                                        | 06/12/2021 | This age group was added to general recommendation for boosting                                                                                                     |
| Maximum of 1 test negative in the follow-up period                                | 06/12/2021 | As the booster period is quite short using up to 4 random negatives is not necessary and using 1 helps ensure independence.                                         |
| Addition of post booster intervals of 14-34,35-69 and 70+ days post vaccination   | 06/12/2021 | More time has now passed to allow potential waning to be assessed.                                                                                                  |
| Change from 140+ days to 175+ days as the comparator follow-up period post dose 2 | 06/12/2021 | The vast majority of boosters given at the time of the study were from 175+ days so this represents a better estimate of the waned post dose 2 level of protection. |

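### Section 3.3 still limits the study population to age 50 and over, which excludes the 18-49 group named in the aim; section 3.9 should also state the age-specific models

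*Protocol*

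**What the plan says.** Four places in the protocol bear on age.

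- Section 3.3 (Study population) reads in full: "All adults resident in England aged 50 years and older reporting symptoms and tested during the study period".
- Section 2.1 (Aim) targets symptoms, "hospitalisation and death in adults aged 18-49 years and 50 years and older".
- Section 3.2 (Data sources) takes PCR tests for people aged 18 and over, "years from the UKHSA Unified Sample Database".
- Section 7 (changes from version 2.1 to 2.2) lists "Addition of 18-49 analysis", dated 06/12/2021, because this age group had been added to the general booster recommendation. Section 1 gives the background: on 30 November 2021 "the booster vaccine programme was rolled out to all individual's aged 18 years and over".

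Section 3.9 (Statistical analysis) opens by giving its target as "vaccine effectiveness of a booster dose of BNT162b2 vaccine against PCR-confirmed symptomatic disease", with hospitalisation and death following. Its only statement on stratification is "Analyses will stratified by which primary doses had been received". Age appears there as an adjustment covariate in 5-year bands.

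**The concern.** The study population statement decides whose tests enter the analysis. If it admits only people aged 50 and over, the 18-49 group is a stated target of the study and outside its population at the same time. An analyst who applies 3.3 produces no 18-49 estimate for any endpoint. An analyst who applies 2.1 and 3.2 produces estimates in people the protocol does not define as eligible.

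Section 3.9 does not settle the matter. It says how the analysis is split by primary course but not how it is split by age. A reader who corrected only 3.3 would still not find a statement that the two age groups in the aim are to be modelled separately.

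**Working it through.** No sample size, power or event figure is involved (section 3.8 gives no numerical sample size), so the check is a comparison of the current text.

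**Age range**

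| Section | Age range stated |
|---|---|
| 2.1 Aim | 18-49 and 50+ |
| 3.2 Data sources | 18+ |
| 3.3 Study population | 50+ |
| 7 Changes, version 2.2 | 18-49 analysis added |

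Section 3.3 is the only one that excludes ages 18-49. It carries a single lower limit and no qualifying phrase, so it cannot be read in a way that admits them. The aim covers 2 age groups and 3 endpoints, or 2 × 3 = 6 combinations of age group and endpoint. Under 3.3 as written, 1 × 3 = 3 remain and the three for 18-49 are lost.

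The conflict does not rest on the change table. Sections 2.1, 3.2 and 3.3 are all current text, and 3.3 disagrees with the other two. The table only suggests the cause: the 18-49 analysis was added in version 2.2 and 3.3 appears not to have been updated with it.

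**Age in the model**

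Section 3.9 names one stratification factor, the primary course. Age enters as a covariate, and no interaction between age and vaccination status is listed. Covariate adjustment of this kind removes confounding by age but yields one odds ratio across whatever ages are in the model. Estimates for 18-49 and 50+ require either separate fits or an interaction. The same model, with 5-year bands, can be fitted within each age group, so 3.9 is compatible with the aim. It simply does not say that this will be done.

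**Booster vaccine**

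- Section 2.2: all three primary objectives cover each booster vaccine.
- Section 3.5: groups IV and V define half-dose Moderna boosters after BNT162b2 and after ChAdOx1-S, each at 7-13 days and at 14 days or more.
- Section 3.9: vaccination status is the exposure term, and 3.5 subdivides that status to include IV and V.
- Primary analysis: refers to boosters in general.
- Section 3.9, opening sentence: names BNT162b2 only.

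One introductory sentence is narrower than the four other places. The Moderna comparison is specified without it.

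**The case against.** The strongest reply is that the intent is plain. The aim, the data extraction, the 18+ roll-out in section 1 and the change table all point the same way, and 3.3 looks like a sentence missed in an update. No estimate or comparator is shown to be wrong, and the repair is a matter of wording. The description of the cause is probably right. It does not remove the point, because 3.3 is the operative population definition and following it removes a target group.

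On section 3.9, the reply is that silence is not contradiction. The stratification sentence does not say that primary course is the only stratum, and detail of this kind may sit in a statistical analysis plan that is not at hand. That stands. The age-specific models are therefore a companion edit and not a second contradiction.

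A reader might go further and infer two things that the protocol does not support.

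- *That 18-49 and 50+ will be pooled into one all-adult estimate, biased by the selective early eligibility of the younger group.* No section proposes such an estimate; the aim names two groups and the change table speaks of an 18-49 analysis. Section 3.9 also adjusts for calendar week, health and social care worker status, clinical risk group, clinically extremely vulnerable status and severe immunosuppression. These cover much of the early eligibility listed in section 1, though carers and household contacts of immunosuppressed people are not among the covariates.
- *That the Moderna objectives are not delivered.* Sections 2.2 and 3.5, the exposure term in 3.9 and the primary analysis all provide for them.

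**Conclusion.** The contradiction on age is real and should be corrected. Section 3.3 conflicts with sections 2.1 and 3.2, and read literally it excludes one of two target age groups for all three endpoints. That size assumes the population statement is applied as written. If analysts follow the aim instead, the 18-49 estimates will exist but will fall outside the population the protocol defines.

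The absence of age strata from 3.9 is a gap worth closing in the same edit. The BNT162b2-only phrase is a minor inconsistency of wording with no analysis lost. No bias in any estimate has been shown.

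**What to change.** 1. In section 3.3, change the age limit to *aged 18 years and older*.
2. In section 3.9, state that the models are fitted separately in 18-49 and 50+, as well as by primary course, with 5-year age bands inside each age group.
3. As a minor correction, reword the opening sentence of 3.9 so that it covers both booster vaccines, BNT162b2 and half-dose mRNA-1273.

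The cost is three wording edits. No new extraction is needed, since section 3.2 already draws tests from age 18. Separate age-specific fits give wider intervals in any sparse cells. The protocol gives no counts, so how many cells would be affected cannot be said.
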